**Fig. 2 Fig2:**
[figure not shown]
Schedule of enrolment, interventions and assessments for the study Safe Birth and Cultural Safety

Control communities receive usual healthcare services. Usual perinatal care for indigenous women in the Montaña region of Guerrero is provided by Western physicians (54.6%), nurses (4.2%) and traditional midwives without external support (20.7%); however, some 20.5% of these women do not have any antenatal care. Among those who received antenatal care, more than 3 out of ten women received less than five antenatal check-ups, the minimum indicated by Mexican standards [37].

In this region, Western physicians (36%), nurses (8%) and traditional midwives without external support (47.9%) provide usual care for childbirth. Some 8.1% of the indigenous women had other or no source of care [37]. Control municipalities have a healthcare centre (*hospital básico comunitario*) in San Luis Acatlán as well as two rural posts (*centro de salud rural* and *unidad de consulta externa*) in Atlixtac. In both cases, healthcare facilities are located in the population centres and provide services for the entire municipality. Women in remote areas need several hours’ walking or travel by gravel road to reach the closest healthcare facility. Regional general hospitals (Ometepec and Tlapa) attend the complicated cases remitted from these communities [38].

The intervention will become obvious to residents in the intervention sites, and some outcomes (particularly social cohesion) could be influenced by knowledge of intervention status. The main outcome indicators (non-inferiority for morbidity and maternal mortality) and other secondary outcomes would be less susceptible to this bias.

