**Methods:**

The study includes four indigenous populations in the State of Guerrero (*Nahua*, *Na savi*/Mixteco, *Me’phaa*/Tlapaneco and *Nancue ñomndaa*/Amuzgo), covering approximately 8000 households. A parallel-group cluster-randomised controlled trial will compare communities receiving usual care with communities where traditional midwives received support in addition to the usual care. The intervention was defined in collaboration with participants in a 2012 pilot study. Supported midwives will receive a small stipend, a scholarship to train one apprentice, and support from an intercultural broker to deal with Western health personnel; additionally, the health staff in the intervention municipalities will participate in workshops to improve understanding and attitudes towards authentic traditional midwives. A baseline and a final survey will measure changes in birth and pregnancy complications (primary outcomes), and changes in gender violence, access to healthcare, and engagement with traditional cultural activities (secondary outcomes). The project has ethical approval from the participating communities and the Universidad Autónoma de Guerrero.

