### Objectives

The overall objective is to reduce maternal morbidity and mortality in indigenous communities without further marginalising or undermining their cultures. The overall hypothesis is that recovery and strengthening of traditional healthcare have a positive impact on indigenous people’s health. An explicit intention is to develop an intercultural approach that reduces the dependence on external resources and promotes the cultural assets of indigenous communities.

Specific objectives of the study are: (1) to assess the impact on maternal health outcomes of a co-designed intervention to support traditional midwives in four municipalities of Guerrero; (2) to assess the secondary or social outcomes of this intervention, including gender violence against pregnant women and behaviours related to traditional midwives; and (3) to evaluate the economic cost of the intervention.

Research question: Among the four main indigenous groups in Guerrero, does support for authentic traditional midwives lead to non-inferior maternal health outcomes and improved social outcomes within the study period, when compared with usual care?

Theory of change: Intercultural brokers increase effective contact with Western health services; this improved referral generates better maternal outcomes by allowing obstetric attention to focus on those who need it most. Better maternal outcomes, along with the apprentices and economic support provided by the intervention, increase prestige of traditional midwives within the communities. Midwives’ prestige promotes cultural continuity and strengthens the social fabric. Additionally, this prestige expands their services among women who do not need specialist obstetric intervention, thus decreasing pressure on poorly funded healthcare services. The no-longer-overloaded healthcare services are then better able to deal with emergency cases and those in need of Western obstetric care, which further improves maternal outcomes.

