### Outcome measures

For objective (1), the central concern is the added benefit of supporting traditional midwives in a context of non-inferior maternal and neonatal mortality. The limited size of the populations involved hinders mortality estimates and increases reliance on intermediate outcomes: birth problems among survivors of pregnancy in the past year. We will measure maternal mortality and morbidity and neonatal mortality through direct questions in each household.

Secondary outcomes (objective (2)) include (a) reduction of social disruption, indicated by gender violence against pregnant women and (b) improvement in intermediate outcomes towards more engagement of women in their culture of origin. The CASCADA model describes these intermediate outcomes in a results chain based on the theory of planned behaviour, overcoming the well-documented limitations of the Knowledge, Attitude and Practices (KAP) model [39, 40]: *C*onscious knowledge, *A*ttitudes, positive deviation from *S*ubjective norms, intentions to *C*hange behaviour, *A*gency (individual and collective), *D*iscussion/socialisation of possible action and, finally, *A*ction or change of practice [41]. Two randomised trials in Pakistan and Mexico, a cross-sectional study in Southern Africa, and a qualitative analysis of narratives in three Southern African countries have used the CASCADA model [42–46].

In this case, the CASCADA model will reflect conscious knowledge of the traditional midwife, a positive attitude about using her services, a positive deviation from a negative subjective norm about traditional midwifery, intention to change in a future pregnancy, the agency to implement these choices, discussion of the choices with partners and, ultimately, interaction with the supported traditional midwife.

The economic outcome measures (objective (3)) are described below under ‘Economic analysis’.

The study will have two measurement points: a baseline survey administered by trained bilingual indigenous interviewers (February and March 2015) and a follow-up survey using the same procedure and questions about pregnancy experiences and outcomes to women pregnant during the past year (May 2017). The period of inquiry for the final survey is defined to avoid any overlap with the pre-intervention period. Given the extent of the region, logistical constraints mean it is not feasible to have continuous or mid-term data collection.

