### Sample size calculation

Borrowing from the field of bioequivalence, equivalency trials and their statistical testing procedures focus on non-inferiority margins [53]. We expect that supporting traditional midwives does not result in worse primary outcomes of maternal health than does the available usual care in the region, principally because so few indigenous women in the study area access available services. Under the non-inferiority hypothesis, the trial might show equivalent or superior effects of the intervention [54]. The pilot study suggested additional benefits that secondary outcomes accrue from a culturally safe intervention. In the absence of previous studies in similar settings, we established a practical margin for non-inferiority-based discussion of findings with local authorities and indigenous communities. The resulting computation of study power illustrates the possibilities of demonstrating non-inferiority in these small communities of fixed size.

Based on 2013 data, we expected 5752 births across the four municipalities [55]. This study size is too small to use maternal mortality as an outcome over the funded duration of the trial, using 150% as the minimum non-inferiority margin to be detected. For birth complications as primary outcome, this study size can detect differences within a practical margin for non-inferiority of 15%, with 80% power at a significance level of 5% (Fig. 4).

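### The primary outcome differs between sections, and maternal mortality is kept as a main non-inferiority indicator although the sample size section says the trial is too small for it

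*Protocol article*

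**What the plan says.** The protocol article describes its main outcome in six places:

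- **Abstract, Methods:** two outcomes, "changes in birth and pregnancy complications (primary outcomes". Mortality is not among them.
- **Objectives:** the research question asks, in general terms, "does support for authentic traditional midwives lead to non-inferior maternal health outcomes and improved social outcomes within the study period".
- **Methods, The intervention (after Fig. 2, on awareness of allocation):** "The main outcome indicators (non-inferiority for morbidity and maternal mortality) and other secondary outcomes would be less susceptible to this bias".
- **Outcome measures:** objective 1 is placed "in a context of non-inferior maternal and neonatal mortality". The small population then "increases reliance on intermediate outcomes: birth problems among survivors of pregnancy in the past year".
- **Principal analysis:** refers to primary outcomes in the plural without naming them, and plans one-sided 97.5% intervals for non-inferiority.
- **Sample size calculation:** "This study size is too small to use maternal mortality as an outcome over the funded duration of the trial". Birth complications are then called the primary outcome, with a 15% margin, 80% power and a 5% significance level.

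**The concern.** A non-inferiority conclusion attaches to a named outcome and a margin. Here a reader can take the primary to be birth complications, birth and pregnancy complications, morbidity and maternal mortality, or maternal and neonatal mortality, depending on the section. Two of these statements cannot both stand: maternal mortality is a main non-inferiority indicator in one section, and in another the study is declared too small to use it.

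Two things are at stake. The confirmatory claim can be chosen after the data are seen. And a statement that support for midwives is non-inferior on mortality could be published on the strength of text that the protocol itself contradicts. In addition, the working outcome covers survivors only, so a woman who dies leaves the outcome that is meant to show safety.

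**Working it through.** **1. Which outcomes have a margin?**

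| Outcome | Where it is primary or main | Margin stated |
|---|---|---|
| Birth complications | Abstract; Sample size calculation | 15% |
| Pregnancy complications | Abstract | none |
| Maternal mortality | The intervention; Outcome measures | 150%, but declared too small to use |
| Neonatal mortality | Outcome measures | none |

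Only birth complications have both a margin and a power statement that the protocol stands by.

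**2. The plan's own power figure.** The 80% power at a 15% margin cannot be strictly reproduced. The sample size section gives no control rate or clustering measure for birth complications, does not say whether 15% is relative or absolute, and does not give the sidedness of the 5%; Fig. 4 is not shown. As an illustration, assume the pilot control rate, 57/248 = 23.0%, a relative margin of 0.15 × 23.0 = 3.4 points, 5752/2 = 2876 births per arm, and one-sided 2.5%:
- ignoring clustering, power is 87%;
- with 40 areas per arm and a between-cluster coefficient of variation of 0.10, power is 80% (87% to 52% for 0.011 to 0.25);
- with two municipalities per arm, power is 39% at 0.011 and 13% at 0.10.

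The stated figure is therefore neither confirmed nor refuted, and the point does not depend on it.

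**3. Error rate if any one outcome suffices.** At one-sided 2.5% each, assuming independence:
- two outcomes: 1 − 0.975² = 0.049
- three: 1 − 0.975³ = 0.073
- four: 1 − 0.975⁴ = 0.096

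**4. Power if both must succeed.** There is then no inflation, but power falls. Take the pilot control rate for pregnancy complications, 65/252 = 25.8%, and assume the same relative 15% margin, which the protocol does not give. Unclustered power for that outcome is 92%. Under independence, joint power is 0.874 × 0.918 = 0.80, against 0.87 for birth complications alone.

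**5. Mortality.** At the cited 281 per 100,000, expected maternal deaths are 0.00281 × 2876 = 8.1 per arm. The analysis section plans risk differences. With 8 deaths in each arm, p = 8/2876 = 0.00278, and the upper 97.5% bound without clustering is 1.96 × √(2 × 0.00278 × 0.99722 / 2876) = 0.0027, or 0.27 points. The 150% margin has two readings:
- a 150% increase: 1.5 × 0.278 = 0.42 points. The bound lies inside it, and power for equal rates is about 86%.
- 1.5 times the control rate: 0.5 × 0.278 = 0.14 points. The bound lies outside it, power is 17%, and about 22,300 births per arm would be needed for 80%.

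The second reading agrees with the protocol's judgement that the study is too small. Under the first, that judgement must rest on clustering or on other inputs not shown.

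**6. Restriction to survivors.** If all 8 deaths in an arm were among women with complications and were dropped, 661/2876 = 23.0% becomes 653/2868 = 22.8%, a fall of about 0.2 points. The ceiling is the death rate itself, 0.28 points. Against an assumed relative margin of 3.4 points this is small.

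**The case against.** The strongest reply is that the protocol does contain one testable primary claim. The sample size section names birth complications with a margin, power and significance level, and Outcome measures explains why the trial moves from mortality to birth problems. The sentence about main outcome indicators is an aside on awareness bias, not a definition. A rule for co-primary outcomes is also commonly left to an analysis plan, which is not shown here.

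Much of this stands. A reader might infer that the trial has no testable primary claim at all; the sample size section shows that it has one. What remains is that this claim is not carried through. The abstract names two primaries, the aside names mortality, and the analysis section keeps an unnamed plural. An analysis plan could not settle this without overriding one part of the protocol.

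Other stronger readings also lack support:
- **That equal mortality would fail the 150% margin.** On the planned risk-difference scale and before clustering, 8 against 8 deaths falls inside a 150% increase. It fails only if 150% means 1.5 times the control rate, and the text does not say which is meant.
- **That the error rate is inflated.** This holds only if either outcome suffices. The protocol does not say so, and requiring both would not inflate it.
- **That the pilot shows one favourable and one unfavourable outcome to choose between.** Pregnancy complications were similar in the two groups (24/94 = 25.5% against 65/252 = 25.8%; OR 0.99). A point estimate near equality is what non-inferiority expects, although the estimate is imprecise.
- **That restricting to survivors could decide the result.** The effect is 0.2 to 0.3 points, and maternal deaths are asked about in each household, so they are not lost to the trial.

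**Conclusion.** The inconsistency is real and lies in the current text. The abstract, the intervention section, Outcome measures and Principal analysis do not agree with the one primary outcome that Sample size calculation names and sizes. The mortality non-inferiority wording conflicts directly with the protocol's own statement about study size.

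The size of the harm is conditional. The error rate is up to about 4.9% with two primaries if either suffices and they are independent. The survivor restriction moves the rate by about 0.2 to 0.3 points, taking 281 per 100,000, 2876 births per arm and, for the lower figure, the pilot control rate of 23.0%. The main consequence is that the confirmatory claim is left open to choice and that a mortality claim the protocol disowns stays in the text. This should be corrected, but it does not leave the trial without a usable primary.

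**What to change.** Before the May 2017 follow-up survey:

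1. Name birth complications as the single primary non-inferiority outcome in the abstract, the intervention section, Outcome measures and Principal analysis, to match Sample size calculation.
2. Make pregnancy complications a secondary outcome.
3. Remove the mortality non-inferiority wording from the intervention section and Outcome measures. Report maternal and neonatal deaths descriptively by arm, with exact intervals.
4. Add a sensitivity analysis that counts every maternal death found in the household survey as an event, including women who died undelivered. Restricting it to pregnancies that reached delivery would bring back the same selective loss. A new composite primary is not needed.
5. Notify the trial registry, as the protocol already provides for changes.

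The cost is wording and one derived variable from data already planned for collection. The protocol is dated 28 February 2017, so the change can be made before follow-up data exist. What is given up is a mortality non-inferiority claim and a second primary, neither of which the trial has been sized to support.

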### Outcome measures

For objective (1), the central concern is the added benefit of supporting traditional midwives in a context of non-inferior maternal and neonatal mortality. The limited size of the populations involved hinders mortality estimates and increases reliance on intermediate outcomes: birth problems among survivors of pregnancy in the past year. We will measure maternal mortality and morbidity and neonatal mortality through direct questions in each household.

Secondary outcomes (objective (2)) include (a) reduction of social disruption, indicated by gender violence against pregnant women and (b) improvement in intermediate outcomes towards more engagement of women in their culture of origin. The CASCADA model describes these intermediate outcomes in a results chain based on the theory of planned behaviour, overcoming the well-documented limitations of the Knowledge, Attitude and Practices (KAP) model [39, 40]: *C*onscious knowledge, *A*ttitudes, positive deviation from *S*ubjective norms, intentions to *C*hange behaviour, *A*gency (individual and collective), *D*iscussion/socialisation of possible action and, finally, *A*ction or change of practice [41]. Two randomised trials in Pakistan and Mexico, a cross-sectional study in Southern Africa, and a qualitative analysis of narratives in three Southern African countries have used the CASCADA model [42–46].

In this case, the CASCADA model will reflect conscious knowledge of the traditional midwife, a positive attitude about using her services, a positive deviation from a negative subjective norm about traditional midwifery, intention to change in a future pregnancy, the agency to implement these choices, discussion of the choices with partners and, ultimately, interaction with the supported traditional midwife.

The economic outcome measures (objective (3)) are described below under ‘Economic analysis’.

The study will have two measurement points: a baseline survey administered by trained bilingual indigenous interviewers (February and March 2015) and a follow-up survey using the same procedure and questions about pregnancy experiences and outcomes to women pregnant during the past year (May 2017). The period of inquiry for the final survey is defined to avoid any overlap with the pre-intervention period. Given the extent of the region, logistical constraints mean it is not feasible to have continuous or mid-term data collection.

The surveys will use instruments tested during the pilot study and will include questions about: maternal deaths, neonatal deaths, number of times women are seen by the traditional midwife during pregnancy, proportion of births at home attended by midwives or without external assistance, frequency of recourse to the traditional midwife in case of pregnancy complications, frequency of recourse to the traditional midwife in case of complications with newborns, proportion of women intending to have future births at home, infection postpartum, and cost of birthing. Among women who gave birth in health institutions, we also will ask questions about their treatment, including birth position, availability of translators, presence of family members at the birth, presence of the traditional midwife at the birth, bathing in cold water, treatment of the placenta, retention of amulets, and how respectful they consider their treatment to have been.

Secondary outcomes measured in the follow-up survey will include: prevalence of violent acts towards pregnant women, opinion as to whom the woman should consult first when she learns that she is pregnant, opinion of who should attend to the woman first if she has complications during pregnancy, opinion as to who should decide whether to take the woman to the hospital if there are complications during childbirth, perception of neighbours’ preferences as to who should provide antenatal care, perception of neighbours’ preferences as to home vs institutional birth.

A qualitative mid-course peer evaluation using the Most Significant Change technique with local stakeholders will provide information about progress and the relevance of secondary outcomes regarding cultural safety [47]. This technique is a participatory method for monitoring and evaluation of complex projects in which participants narrate stories describing the most significant changes they attribute to the intervention, and implementers review the stories. This will provide information about change dynamics, identify issues in implementation and provide moral support for the intercultural brokers*.*

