### The intervention

The intervention has four components that incorporate the co-design exercise from the pilot study and subsequent discussions with the midwives in the four indigenous groups. The intervention comprises activities to invigorate the practice of traditional midwifery and increase the interaction of traditional midwives with the Western healthcare system. The intervention does not define a protocol for the management of motherhood in these communities; thus, Western physicians and traditional midwives remain autonomous in their own practice.

Component 1. Material support for 30 authentic traditional midwives. Each traditional midwife in the intervention group will receive a monthly stipend of US$20. This small financial support is meant to allow the traditional midwives access to basic goods and increase the time that they have available for their practice and patient care; most of these traditional practitioners are low-income elderly depending on their own work or on support from their families. Additionally, the small monthly payment will be a symbol of external esteem for the role of these traditional midwives, thus increasing their recognition among community members. Field coordinators will be in charge of the payments to the traditional midwives in the intervention municipalities.

Component 2. Scholarship support of one apprentice for each midwife. The midwives in the intervention group will each appoint one apprentice to receive a monthly stipend of US$10; the midwife will decide on the training programme and the criteria to evaluate the achievements of her apprentice. The midwife will authorise the payment for the apprentice, while the field coordinators will be in charge of the disbursement. The apprentices will support the practice of the traditional midwives, particularly in tasks that the midwives can no longer perform due to their age. This component will foster the intergenerational transfer of traditional midwifery practice and increase its recognition by community members.

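### The last CASCADA step (Action) is worded as contact with the supported midwife, which if scored as written cannot be compared fairly between arms or with baseline

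*Protocol article*

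**What the plan says.** The protocol article, under Outcome measures, makes women's engagement with their culture of origin secondary outcome (b) and describes it through the seven-step CASCADA results chain. In its general form, the last step is an action or a change in practice and is tied to no arm.

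The section then gives the trial-specific content. It opens in general terms: "the CASCADA model will reflect conscious knowledge of the traditional midwife, a positive attitude about using her services". It closes with "discussion of the choices with partners and, ultimately, interaction with the supported traditional midwife". The word *supported* appears only at this last step.

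Support belongs to one arm. Under The intervention: "Each traditional midwife in the intervention group will receive a monthly stipend of US$20". The apprentice scholarship also goes to intervention-group midwives. For usual care, which is what control communities receive, the same section says: "Western physicians (36%), nurses (8%) and traditional midwives without external support (47.9%) provide usual care for childbirth".

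The survey content listed later under Outcome measures is not restricted in this way. One item is "number of times women are seen by the traditional midwife during pregnancy". Others cover home births attended by midwives and recourse to the traditional midwife when complications arise.

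**The concern.** Objective 2 covers behaviours related to traditional midwives, and the research question asks whether social outcomes improve in comparison with usual care. The CASCADA steps are therefore meant to be compared between arms. Action is the end of the chain and the step that records what women actually do.

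A control woman looked after throughout by an authentic traditional midwife has done what the outcome is meant to capture. Under the trial-specific wording she would not count, because her midwife is not a supported one. An intervention-arm woman with the same behaviour, seeing a midwife who now receives a stipend, would count. The step would then partly measure delivery of the programme and not behaviour. The trial could report more engagement with traditional midwifery when existing care had only acquired a new label.

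**Working it through.** The article states no figure for this step, so there is none to reproduce. The check compares the wording across sections and then does simple arithmetic.

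**1. Can the control arm reach the step as worded?** The stipend and apprentice go to intervention-group midwives, and usual-care midwives are described as having no external support. A control woman could meet the wording only by travelling to a supported midwife in another municipality. Under Random allocation of the intervention, whole municipalities are randomised in order to avoid that kind of crossover. The expected control value is therefore near zero, though not necessarily exactly zero.

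**2. Can it be reached at baseline?** The baseline survey was in February and March 2015. The broker course ran in May and June 2015 (Table 1), and the intervention starts after it. No midwife was yet supported by this trial at baseline, so change from baseline in the literal step has no useful meaning.

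**3. Which other steps share the problem?** The other six (knowledge, attitude, deviation from the subjective norm, intention, agency, discussion) are worded for the traditional midwife or traditional midwifery in general. Both arms can reach them.

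**4. Do the survey items settle the definition?** They can be answered in both arms, and the follow-up is to use the same questions on pregnancy experiences as baseline. The article does not link them to Action. Its separate list of secondary outcomes for the follow-up survey contains violence, opinions and perceived neighbours' preferences, with no item on contact with a midwife.

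**5. Size of the possible artefact.**

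Inputs:
- Share of births attended by unsupported traditional midwives under usual care: 47.9% (The intervention, usual-care paragraphs; Montaña region).
- Share of antenatal care given by them: 20.7% (same place).
- Share *s* of intervention-arm midwife users who see a supported midwife: not given, so assumed to be 25% to 100%.
- True difference in midwife use between arms: set to 0.
- Control contact with supported midwives: taken as 0.

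Spurious difference under the literal wording = usual-care share × *s* − 0.

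| Setting | *s* = 25% | *s* = 100% |
|---|---|---|
| Childbirth | 47.9 × 0.25 = 12.0 points | 47.9 × 1 = 47.9 points |
| Antenatal | 20.7 × 0.25 = 5.2 points | 20.7 × 1 = 20.7 points |

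Under a definition that counts any traditional midwife, the expected difference is 47.9 − 47.9 = 0 points for childbirth and 20.7 − 20.7 = 0 points for antenatal care.

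**The case against.** The strongest reply is that a single adjective in a descriptive sentence is being read as a coding rule. The sentence says what the model reflects and sets no numerator. The general definition of Action is neutral between arms, and so is the start of the same sentence. Every listed survey item on midwife contact is generic, so on those items a control woman who uses a traditional midwife is counted and the baseline is not zero. The related skilled-attendance outcome, under Sample size calculation, also counts any traditional midwife or physician. The article is condensed, and neither the questionnaire nor any analysis plan is shown.

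Much of this stands. A reader might infer that the control arm scores zero by construction and that the comparison therefore proves nothing. The documents do not support that. No scoring rule limited to supported midwives is shown, the available items would give a valid comparison, and crossover could lift the control value slightly above zero. It would also be wrong to extend the criticism to the knowledge step, whose wording is already general.

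One part does not stand. The sentence is the article's only trial-specific statement of what Action means, and it uses a term that elsewhere separates the arms. The generic items show that a sound measure is available, but not that it was chosen. The two parts of Outcome measures disagree on what is counted, and that goes beyond a detail left to a fuller document.

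**Conclusion.** The point holds as a badly fixed definition of one of the seven steps of a secondary outcome. If Action is scored as worded, it is near zero in control communities and at baseline, and cannot be compared fairly between arms or over time. With no true change in behaviour, the artefact would be about 12.0 to 47.9 points for childbirth or 5.2 to 20.7 points for antenatal care.

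These ranges rest on three assumptions: the Montaña shares apply to both arms, 25% to 100% of intervention-arm midwife users see a supported midwife, and control contact with supported midwives is negligible. The upper ends are worst cases. Whether the step will in fact be scored this way cannot be confirmed from the article. The other six steps, the gender-violence outcome and the primary outcomes are not affected.

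**What to change.** Define Action as contact with any authentic traditional midwife, supported or not, during pregnancy or birth. Name the existing survey items on midwife contact as its measure, and apply them in identical form in both arms and in both surveys. Report contact with a supported midwife separately, as an uptake measure in the intervention arm only. The knowledge step needs no change.

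For the Action step the cost is a change of wording, since the items are already in the survey. The listed items do not say whether the midwife was supported, so the uptake measure may need one added question if the questionnaire does not already identify her. The apparent effect on this step will be smaller, but it will reflect what women do.
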